# Protocol for evaluating the effects of integrating music with taekwondo training in children with autism spectrum disorder: A randomized controlled trial

**DOI:** 10.1371/journal.pone.0315503

**Published:** 2025-01-31

## Abstract

**Background:**

Children with autism spectrum disorder (ASD) are known to experience difficulties in coordinating fine- and gross-motor movement. Previous interventional studies have reported significant effect of exercise-based intervention programs on improving motor skills and alleviating symptoms in ASD; however, researchers are yet to know why some participants experienced less improvement than others. One plausible explanation for suboptimal treatment outcomes is insufficient engagement in the exercise programs due to the children’s difficulties in following instructions and performing the correct movements. In the proposed research, we will test the above speculation by manipulating the amount of music-therapy elements into a 10-week Taekwondo training program designed specifically for children with autism.

**Methods:**

This is a randomized controlled trial. Seventy-two children aged 7 to 9 years who meet the diagnostic criteria of ASD will be recruited and randomized into either the “Taekwondo training with elements of music therapy” group or the “Taekwondo training alone” group. In both groups, the participating children will attend Taekwondo training sessions twice a week over 10 consecutive weeks. In the “Taekwondo training with elements of music therapy” group, elements of music therapy will be incorporated into the Taekwondo training. Assessment will be conducted before the program commences, immediately after the completion of the 10-week program, and 2 months after the post-test. The outcome domains to be evaluated include the immediate effects during the exercise sessions. These effects include the level of engagement in the exercise sessions (primary outcome), enjoyment, physical activity level, and rate of perceived exertion. Furthermore, the evaluation will also cover the overall effects of the training program on gross motor skills, Taekwondo skills performance, executive function, psychosocial functioning, and behavioral problems.

**Discussion/Findings:**

The findings of this study will inform strategies for the promotion of physical activity and engagement among children with ASD when participating in exercise training classes. The study will also suggest the importance of regular physical activity for the physical and mental well-being of children with ASD.

**Trial registration:**

**Clinical trial registration:** URL: http://www.clinicaltrials.gov. ClinicalTrials.gov Identifier: NCT06277778. Registered on 15 February 2024.

## Introduction

ASD is a developmental disability characterized by persistent impairments in social interaction, communication, and behavioral functioning [1]. Studies in Asia, Europe, and North America have identified an average ASD prevalence of 1.5% in their populations and have projected an increasing trend [2]. In addition to the core features of autism, motor impairments are highly prevalent in children with ASD. The prevalence of gross motor skills deficits, such as reduced balance and coordination, in children with ASD is 21% to 100% [3]. In children with ASD, impaired motor skills are significantly related to social communication skill deficits [4], emotional or behavioral disturbance [4,5], as well as decreased physical activity levels [6,7]. Deficiencies in motor control and a lack of engagement in physical activities often result in inferior physical health and higher susceptibility to chronic diseases. Notably, obesity is highly prevalent among children with ASD [8].

Studies in the last two decades have demonstrated that exercise not only improves motor skills but also attention, social cognition, and psychological well-being in children with ASD [6,9]. For example, Toscano et al. reported beneficial effects on metabolic indicators, autism traits, and parent-perceived quality of life in 6-to-12-year-olds with ASD following an exercise program [10]. However, most studies have employed exercise involving repetitive body movements (e.g., running on a treadmill), which could induce boredom. Therefore, we propose the inclusion of multi-dimensional training elements to provide all-round training on different types of motor skills, which is crucial for ASD children [11]. Taekwondo training is a good option for quantifying children’s skills learning, as evidenced in our preliminary studies. Past studies have indicated that Taekwondo training improves balance control and isokinetic muscle strength in children with ASD [12] as well as developmental coordination disorder [13], but its effects on Taekwondo skills learning and mental conditions of children with ASD remain unknown. Taekwondo, a combat sport with a long history, generally involves punching, kicking, sparring, breaking, self-defense techniques, and Poomsae (a combination of offensive and defensive movement sequences). Apart from the repetitive movements of the large muscle groups, the speed and accuracy of the kicks and strikes are drilled. Moreover, mastery of Taekwondo requires strong balance and coordination, muscle strength, and a high level of tolerance, self-control, and focus on tasks.

However, children who cannot engage actively in an exercise program may experience less improvement than anticipated. Factors contributing to the lack of engagement are multifactorial. In a survey, a group of physical educators identified inattention, social impairment, emotional regulation difficulties, and inflexible adherence to routines and structure were identified as teaching challenges [14]. We speculate that the integration of music therapy into an exercise program is a potential solution to these challenges.

Music therapy is the clinical and evidence-based use of music interventions by a credentialed music therapist to accomplish individualized goals, such as addressing the physical, emotional, cognitive, and social needs of the patient. Although children with ASD may exhibit impaired social and verbal communication, their musical skills are generally intact [15]. For example, they often demonstrate good pitch and timbre processing abilities, enhanced melodic memory, and large rhythm synchronization capacity [16], as confirmed by neuroimaging studies. For example, Sharda et al. revealed that, although speech processing is impaired in children with ASD, their song perception remains intact despite the two processes being operated by similar functional neural networks [17]. Previous studies have reported that music therapy interventions are associated with increased engagement behavior [18], emotional engagement [19], joint attention (the ability to share a focus on an object or area with another person) [20], and peer interactions [21]. However, many of these studies were clinical reports, case studies, and single-group studies with low generalizability [22,23]. In another study, Sharda et al. conducted a randomized controlled trial on music-based interventions using songs and rhythm for children with ASD. The authors demonstrated that 8–12 weeks of individual music intervention improved the children’s auditory and visual attention responses, social communication, and functional brain connectivity [24]. However, studies examining the effects of music during exercise training on improving attention, active engagement, and social communication in children with ASD are scarce.

Furthermore, different musical elements may have specific influences on exercise interventions for children with ASD. For example, one study documented that musical rhythmic accompaniment enhanced gross motor performance [25]. Another study reported that slow music may motivate young children with ASD to engage in vigorous exercise [26]. We speculate that if different songs are paired with specific Taekwondo movements in the training sessions, the music could serve as useful cues, allowing children to anticipate the next movement upon hearing a particular song. Our study will apply the collaborative and consultative music therapy approach, which involves training the trainers to employ music therapy principles effectively to maximize the training’s effectiveness [21]. The music therapist will provide guidance and training to the Taekwondo coaches, enabling them to standardize their instructions to the children according to the rhythm of different music used in the program.

According to Karageorghis’s (2016) model, musical factors (e.g., tempo, rhythm, melody, and harmony) can be considered the antecedents that interact with the moderators (e.g., sound intensity and exercise intensity) to determine an individual’s response to a piece of music. The model predicts beneficial physical and psychological outcomes associated with music used in exercise and sports [27]. In line with this model, research studies have shown that integrating music into exercise promotes pleasure and diverts attention away from the unpleasant bodily sensations generated through strenuous exercise [27,28]. Moreover, the rhythm of music can trigger the firing rate of auditory neurons. This, in turn, drives the firing patterns of motor neurons, resulting in auditory-motor synchronization—a form of rhythmic entrainment [29,30]. Based on this principle [30,31], we speculate that if the music is selected based on the desired pace and intensity of the Taekwondo training, auditory–motor synchronization during exercise may assist in improving the motor skills of children with ASD.

The insights provided by Srinivasan et al. (2014) and their conceptual framework implicate several causal links between music experiences and the development of language, communication, and social-emotional, behavioral, and motor skills in children with ASD [32]. In addition, Karageorghis’s (2016) theoretical model that addresses the antecedents, moderators, and consequences of music used in the exercise and sports domain [27,33] provided us with a framework for developing a model of combined music therapy and Taekwondo training to improve the physical and mental outcomes of children with ASD (S1 Fig). The predicted immediate effects observed during the exercise sessions include increased engagement and enjoyment, reduced perceived exertion, and increased physical activity level. The predicted overall benefits of Taekwondo training with elements of music therapy include improvements in gross motor skills, Taekwondo skills performance, attention, and social communication and behaviors.

Herein, we propose to test this hypothesis by conducting a randomized controlled trial to evaluate participating children in terms of the aforementioned study outcomes of a 10-week Taekwondo training program, with the presence or absence of music.

This trial has two objectives: (1) to examine the immediate effects of music therapy integrated into Taekwondo training sessions on the engagement and enjoyment during the training sessions in children with ASD; and (2) to examine the effects of a 10-week Taekwondo training program, with the presence or absence of music therapy, on the physical and mental outcomes in children with ASD. We hypothesize that the addition of musical elements specifically designed to match the rhythm and dynamic movement of the Taekwondo training will increase active engagement during the training sessions and provide extra benefits on physical and mental outcomes for children with ASD. The domains to be evaluated include the immediate effects during the exercise sessions of engagement (primary outcome), enjoyment, physical activity levels, and rates of perceived exertion, as well as the overall effects of the training program on gross motor skills, Taekwondo skill performance, executive function, and psychosocial functioning and behavioral problems.

## Methods

### Study design

This study will be a parallel-group randomized controlled trial, conducted and reported according to international standards (CONSORT) (Figs 1 and 2) and was registered as a clinical trial with ClinicalTrial.gov (NCT06277778).

**Fig 1 pone.0315503.g001:**
[figure not shown]
SPIRIT schedule of enrolment, interventions, and assessments of the study.

**Fig 2 pone.0315503.g002:**
[figure not shown]
CONSORT diagram of the trial.

### Participants and study setting

Flyers containing information about the study will be sent to both autism support groups for parents in the community and randomly selected primary schools in Hong Kong. The parents of potential participants who are interested in the study will be invited to attend an introductory session about the project, after which they will be given an information sheet and parental written consent form. Children meeting the following eligibility criteria will be invited to participate in the study:

Inclusion Criteria:

Aged 7 to 9 years, andClinically diagnosed with ASD by a developmental pediatrician or clinical psychologist based on the Diagnostic and Statistical Manual of Mental Disorders (fifth edition)’s criteria for ASD [1].

Exclusion Criteria:

Any experience in Taekwondo training,Received music therapy within the previous 12 months,Learning difficulties and intellectual disabilities,Sensory disorders (blindness or deafness), orUnderlying congenital abnormalities or other diseases that limit their ability to engage in physical activities.

### Randomization and blinding

Block randomization will be implemented for this study, with varying block sizes of 2 to 4, to prevent selection bias and predictability. The randomisation list will be computer-generated and concealed by a researcher (author identifying information) who will have no direct contact with the participants. A research assistant will enroll participants and assign them to either the “Taekwondo training with elements of music therapy” (n = 36) or the “Taekwondo training alone” (n = 36) group in a 1:1 ratio. Given the behavioral nature of the intervention, blinding will not be feasible for the participants and parents. They will be unaware of their group allocation in the recruitment process until they provide written consent. The coaches, the trial coordinators, and the research personnel who review and code the video recording of the training sessions will also not be blinded to the group allocation. There will be concealment of the allocation sequence so that the trial coordinators will not know the group allocation of an individual before they consent them. To minimize measurement bias, all other research personnel involved in data collection, processing, and analysis will be blinded to group allocation.

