### Intervention

In both conditions, the participating children will attend 20 sessions of Taekwondo training. Except for the experimental manipulation (the presence or absence of music), children will receive the same level, skills, and duration of Taekwondo training across both conditions. The training will be administered in a group setting (six children per class), twice a week over 10 consecutive weeks. Each training session will last for 45 minutes and consist of warming-up exercises, hand movements, stance, foot movement techniques, a combination of stance and hand and foot techniques, and cool-down exercises. The teaching syllabus will follow the white belt (most junior) rank of the Taekwondo grading system. A qualified Taekwondo coach will conduct the training alongside a teaching assistant and two student assistants in each session.

In the Taekwondo training with elements of music therapy group, elements of music therapy will be incorporated into exercise training. Each piece of music will be tailor-made according to the rhythm, dynamic, tempo, duration, and associated feeling of a series of Taekwondo movements. For example, when forceful kicking is necessary, music with a rapid rhythm and strong, heavily accented beat will be applied. The music will serve to guide the motor patterns in a feedforward manner. The coaches will provide demonstrations that follow the tempo and rhythm of the specially composed music to guide the children in completing the Taekwondo movements. Short songs will also be composed, recorded, and played to accompany recurrent activities such as deep breathing and movement transitions. These short music pieces will offer cues to the children for recurrent activities and increase their success in effectively following the coach’s lead.

Teaching assistants will document attendance rate and any significant events during the study period. Participants who have been consistently absent will be contacted to investigate the reasons for their absence and to encourage regular attendance. If a participant drops out of the training sessions, they will still be invited to complete the post-training and 2-month follow-up assessments. All kinds of ASD-related concomitant trainings are permitted during the study period and information on these trainings will be recorded.

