### Sample size calculation

A previous study that used jogging as an exercise format in a group of children with ASD aged 5 to 13 years demonstrated that the percentage of time the participants spent in vigorous exercise, which correlates with engagement, was significantly higher under the slow-music condition (a tempo of 60, which is similar to the songs developed in this proposal) compared with the non-music condition (mean difference = 11.8%, common SD = 21.6%, effect size d = 0.55) [26]. Another study also revealed that music increased the engagement of students with autism during group activities [18], as the percentage of time in class during which participants exhibited active engagement behaviors increased from 44.7% ± 16.9% to 68.8% ± 13% (effect size d = 1.61). Considering these studies, assuming an effect size (d) of at least 0.55 in the primary outcome proposed for this study (engagement) will be observed for the Taekwondo training with elements of music therapy condition in contrast to the Taekwondo training alone condition, a minimum of 54 subjects are required to detect such an effect with a power of 80% and type I error of 0.05. To account for a 20% attrition rate and the requirement of pairing-up children for practice per group, 72 participants will be recruited in total.

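### Blocks of 2 to 4 do not secure the stated unpredictability if allocation is rolling and consent-takers know earlier allocations; a block of 3 also cannot be split 1:1

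*Protocol article*

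**What the plan says.** All in the Protocol article:

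- **Randomization and blinding, block sizes.** Block randomization is used "with varying block sizes of 2 to 4, to prevent selection bias and predictability". Allocation is 1:1 with 36 children per arm. The Sample size calculation section agrees: "72 participants will be recruited in total".
- **Randomization and blinding, who does what.** A computer-generated list is held by a researcher without participant contact. One research assistant both enrols children and assigns them.
- **Randomization and blinding, who knows the arm.** "The coaches, the trial coordinators, and the research personnel who review and code the video recording of the training sessions will also not be blinded". Concealment is described as keeping coordinators unaware of a given child's group until they have consented that child.
- **Ethical approval.** The research coordinator explains the study and takes parental consent.
- **Intervention.** Training is in groups, with "six children per class".

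The text does not say whether size 3 is used, whether the sizes are withheld from enrolling staff, or whether a whole intake is consented before any arm is revealed.

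**The concern.** Holding the list elsewhere stops staff from reading the next allocation. It does not stop them from inferring it. Short balanced blocks return to equality every few children, so a person who knows the earlier allocations can often tell which arm is due. By the protocol's own account the people who take consent may have that knowledge. If arms are released child by child, staff could time a particular family's consent to suit the arm they expect. The resulting imbalance could lie in traits that adjustment for age, sex and BMI does not reach. In a trial open to families, coaches and coordinators, unpredictable allocation is one of the main safeguards left, and the protocol names it as the purpose of its block sizes.

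The wording of the range adds a second problem. A 1:1 block must have an even size, so a literal range of 2 to 4 includes a size that cannot meet the stated ratio.

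**Working it through.** **Inputs.** From the protocol: 72 children, 1:1 ratio, 36 per arm, block sizes 2 to 4. Assumed: rolling release of arms, a guesser who knows the possible sizes and all earlier allocations but not the size of each block, and all sizes equally likely.

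**1. The plan's own figure.** 72 / 2 = 36. Even blocks on a list that closes at 72 give exactly 36 and 36, so the stated split is reproduced if the sizes are 2 and 4.

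**2. Sizes 2 and 4, by hand.** The best strategy is to guess the arm that lags, and to toss a coin when the arms are level.

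- Block of 2: expected correct guesses are 1/2 + 1 = 1.5 of 2.
- Block of 4, second child: the lagging arm comes up with probability 2/3.
- Block of 4, third child: if the first two match (probability 1/3), the next is certain; otherwise it is a coin toss. That gives 1/3 × 1 + 2/3 × 1/2 = 2/3.
- Block of 4, total: 1/2 + 2/3 + 2/3 + 1 = 2.833 of 4.
- Equal mix: (1.5 + 2.833) / (2 + 4) = 4.333 / 6 = 72.2%, and 0.722 × 72 = 52 children, against 36 by chance.

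The mix matters little: all blocks of 2 give 1.5 / 2 = 75%, and all blocks of 4 give 2.833 / 4 = 70.8%.

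*Certain assignments.* When block sizes are hidden, certainty arises only when a lead of two shows that a block of 4 is half done. That happens in 1/2 × 1/3 = 1/6 of blocks and fixes two children. With a mean block length of 3, the share is (1/6 × 2) / 3 = 11.1%.

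*Strongly predictable assignments.* After one child of a new block, the lagging arm follows with probability 1/2 × 1 + 1/2 × 2/3 = 5/6; after three, it is certain. So every second child is predictable with probability at least 5/6. Adding the certain third places gives 50% + 11.1% / 2 = about 56%.

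**3. Simulation, 4,000 lists of 72.** A block of 3 was taken as equally likely to split 2:1 or 1:2.

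| Sizes | Guessed correctly | Probability at least 0.75 | Certain |
|---|---|---|---|
| 2, 4 | 72.1% (51.9 of 72) | 55.4% | 10.8% (7.8 of 72) |
| 2, 3, 4 | 67.6% (48.7 of 72) | 30.4% | 1.2% (0.9 of 72) |
| 4, 6, 8 | 67.8% (48.8 of 72) | 34.6% | 2.3% (1.7 of 72) |

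The first row agrees with the hand calculation.

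**4. If staff can also tell where blocks end.** A block of 2 has 1 certain child and a block of 4 has 1 + 1/3 = 1.333. The equal mix gives (1 + 1.333) / 6 = 38.9% certain.

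**5. The block of 3.** It can split only 2:1 or 1:2. With sizes 2, 3 and 4, about 73% of lists stopped at 72 are not 36 and 36, and the mean absolute difference between arms is about 2.3 children.

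**6. One-step allocation.** 72 / 12 = 6 intakes, each split 6:6. If all 12 families have consented before the draw, no family's allocation can be predicted when it consents.

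**The case against.** The case for the plan has four parts.

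- **Varying the size does help.** Fixed blocks of 2 would make 36 of 72 assignments certain, against about 8 with sizes 2 and 4. This stands. A reader might infer that most allocations are known in advance; the figures show better-than-chance guessing, with few certainties unless block ends are known.
- **The figures are an upper bound.** They need staff who know the sizes, keep the full ordered history and guess optimally. An article need not report that sizes are withheld. This stands, and is why the figures are conditional.
- **Rolling allocation is not stated.** Classes of six, introductory sessions for parents, and consent before the study commences all fit an intake that is consented before any arm is revealed. Prediction could then not affect enrolment. The text does not settle this: its concealment statement protects only an individual's own allocation up to that individual's consent.
- **The two complaints rest on different readings.** If size 3 is used, the scheme is no more predictable than blocks of 4, 6 and 8. If it is not, the block of 3 is only loose wording. This stands, so the two sets of figures must not be combined.

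Two stronger readings are tempting. A reader might infer that parents complete the baseline SRS-2 and SDQ knowing the arm, because of "They will be unaware of their group allocation in the recruitment process until they provide written consent". That sentence does not say the arm is released at consent, and the schedule, participant flow and assessment figures that would show the order are not available here. A reader might also tie the block sizes to the unblinded video coding of the primary outcome. The protocol discloses that openly; it is a separate matter that block sizes do not change.

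**Conclusion.** The concern holds in a limited form. The protocol claims that its block sizes prevent predictability, but it leaves consent-taking coordinators aware of earlier allocations and does not state that an intake is consented before arms are revealed. If allocation is rolling and staff know the possible sizes, sizes 2 and 4 allow about 72% correct guesses (71% to 75% over any mix of the two), with about 11% certain. Under the literal range the figures are about 68% and 1%, but the ratio cannot hold within a block of 3 and about 73% of lists miss 36 per arm. On either reading the sentence needs changing: for predictability in the first case, for balance in the second. The documents give no basis for estimating how much bias in engagement would follow, and no claim is made about the timing of baseline ratings.

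**What to change.** **Preferred.** Replace the 2 to 4 range by a statement that each intake of 12 is randomised in one step, 6:6, after all its families have consented, and that arms are released only then. This fills one class of six per arm and removes prediction at consent. It costs a new computer list and one protocol sentence, and an intake must be complete before allocation. It assumes that both arms of an intake start together. If the trial already works this way, stating it and correcting the block wording is enough.

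**If allocation must be rolling.** Use larger even blocks of random size, for example 4, 6 and 8, and state that the sizes are withheld from enrolling staff. Compared with sizes 2 and 4, this cuts certain assignments from about 11% to 2%, but correct guesses only from 72% to 68%, or about 3 of 72 children (51.9 − 48.8). The final split may differ slightly from 36 and 36: in the simulation, about 29% of lists stopped at 72 were unequal, with a mean difference over all lists of about 0.6 children. This option reduces the problem; the one-step draw removes it.
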